**Discussion:**

If the episodic memory of SCD improve after the intervention, the study will confirm that rTMS is a promising intervention for cognitive function improvement on the early stage of dementia. This study will also provide important clinical evidence for early intervention in AD and emphasizes the significance that impaired LTP-like cortical plasticity may be a potential biomarker of AD prognosis by demonstrating the predictive role of LTP on cognitive improvement in SCD.

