It is suggested that impairment to synaptic plasticity plays a crucial role in the development and progression of AD (Walsh and Selkoe, 2004; Shankar et al., 2008). According to Mecca et al. (2020) [^11^C]UCB-J PET technology demonstrated significant synaptic loss caused by AD at neocortical areas such as frontal regions. Another study suggest that cerebellar LTP-like cortical plasticity mechanisms are impaired in AD (Di Lorenzo et al., 2020a). Since the discovery of SCD, neuropathological abnormalities in amyloidosis (e.g., reductions in Aβ42 and increases in amyloid tracer uptake) and neurodegeneration have appeared. The latter includes atrophy in the medial temporal lobes and paralimbic and temporoparietal cortices (Rabin et al., 2017). The loss of long-term EM has not only been referred to as merely local damage to the medial temporal lobes, but also to the malfunction of cortical plasticity on the basis of memory processes (Vidal-Piñeiro et al., 2014). Considering the precocious impairment of plasticity mechanisms in AD, researching synaptic mechanisms in patients who show initial signs of memory deficits can effectively identify early functional anomalies, predict disease progression and evaluate the effectiveness of treatments. We, therefore, decided to study the change in LTP-like plasticity induced by SCD treatment with TMS.

The primary objective of our study is to investigate the efficacy of rTMS on EM in patients with SCD. The Auditory Verbal Learning Test-Huashan version (AVLT-H) will be used as the primary outcome measure. We also explore changes in the both neural and behavioral effects (other cognitive domains) after rTMS interventions. The predictive role of the LTP-like plasticity on cognitive improvement in rTMS-treated SCD patients will be studied. We hypothesized that stimulating the left-DLPFC (l-DLPFC) with 10 Hz rTMS can produce beneficial effects on EM in SCD by enhancing LTP-like plasticity.

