### 2.7. Outcome measurements

#### 2.7.1. Primary outcomes

The Auditory Verbal Learning Test-Huashan version (AVLT-H) assessment will be used as the primary outcome to assess EM for our study. The AVLT-H assesses several aspects of verbal EM through a list of 12 words, such as short or long-term delayed recall and recognition. It has been widely used as a semantic categorization memory test in mainland Chinese populations (Li et al., 2016). The AVLT-H scores include AVLT-H immediate recall total score (AVLT-H-IR-S), AVLT-H short-term delayed recall score (AVLT-H-SR-S) with a 5-min delay time, AVLT-H long-term delayed recall score (AVLT-H-LR-S) with a 20-min delay time, AVLT-H total, and AVLT-H recognition score (AVLT-H-REC-S) (Zhao et al., 2012). This test has been proved to be a sensitive diagnostic evaluation of cognitive impairment (Li et al., 2016).

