#### 2.7.2. Secondary outcomes

Other cognitive domain examinations and LTP-like cortical plasticity will also be measured. Overall cognitive function will be assessed using scores from the Montreal Cognitive Assessment Test (MOCA) as well as the Mini-Mental State Examination (MMSE). In addition, the Wechsler Memory Scale -Logical Memory Test (WMS-LM) and digit span test (DST) will be used to assess memory function and attention, respectively. Language function is measured using the scores of the Animal Fluency test (AFT) and Boston Naming Test China version (BNT-C) test. Measures of executive function include the symbol digitized modality test (SDMT) and the trail making test (TMT) parts A and B (Zhong et al., 2021). Time to completion of TMT A and TMT B will be logged and analyzed. In addition, all participants will be asked to complete two computer experiments conducted using E-Prime 2.0 software (Psychology Software Tools Inc., Pittsburgh, PA, United States). The n-back (*n* = 1) task is used to evaluate working memory, while the Go/No-Go task is used to assess inhibitory control ability (Borgwardt et al., 2008; Kumar et al., 2017). The accuracy and response time will be recorded.

The changes of the MEP amplitude will be measured to assess LTP-like cortical plasticity. Twenty consecutive MEPs of 5-s intervals will be evoked by single-pulse TMS at the left motor hotspot of 120% RMT intensity, and the peak-to-peak average value recorded. The whole LTP-like plasticity assessment includes five time points, whereby two baselines before and 5, 10, and 30 min after the intermittent theta burst stimulation (iTBS) protocol. Two baseline measurements are performed 10 min apart, and the subsequent iTBS paradigm is applied if the variation between the two average measurements is < 15%. The iTBS protocol consists of a burst of three stimuli at 50 Hz and repeated at 5 Hz. A 2-s train of this protocol will be repeated every 10 s for a total of 192 s (600 pulses) with 80% RMT over the left hotspot (Huang et al., 2005; Yu et al., 2020).

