### 2.8. Data analysis

SPSS V.23.0 will be used to analyze the data, and levels of statistical significance will be set at *p* < 0.05. For descriptive statistics, the Shapiro–Wilk test will be applied to check for normal probability prior to data entry. Data from the normal distribution will be reported as mean and standard deviation, whereas medians with interquartile ranges will be used to express the non-normal distribution. Categorical variables will be described as frequency as a function of percent. Demographic characteristics and baseline variables will be compared between the two groups using independent samples *t*-test or non-parametric Mann–Whitney test for continuous data, and comparisons of categorical variables using chi square or Fisher’s exact tests. Based on the existing literature, we can determine whether the unbalanced baseline data affect the results and, if so, conduct covariance analysis using the baseline data as covariates to control for the effect of potential confounders. The experiment will be analyzed using intention-to-treat (ITT) and missing data will be interpolated using multiple imputation method.

For normally distributed data, a repeated-measures analysis of variance (ANOVA) will be conducted to evaluate changes in treatment effect between and within groups (group: real vs. sham rTMS) (time: pre-vs. post-treatment). Alternatively, for non-normally distributed variables, we will perform the Wilcoxon signed rank test for within group comparisons, and the Mann–Whitney test will be applied to compare the effect between groups at each time point. In addition, we also aim to use a repeated-measures ANOVA to examine LTP-like plasticity as a function of percent change at four time points (last baseline, 5, 10, and 30 min after iTBS) between the two groups. *Post hoc* comparisons between groups will be used using the Bonferroni correction method. The generalized linear model (GLM) will be considered if the data is not normally distributed. To investigate the relationship between brain measurements and clinical cognitive function characteristics, we will perform correlation analyses by repeated measures linear regressions.

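### The abstract promises to demonstrate that LTP predicts cognitive improvement, but the only analysis behind it is an open set of regressions at p < 0.05 with no multiplicity rule

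*Protocol article*

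**What the plan says.** The abstract's Discussion says that the study will support impaired LTP-like plasticity as a possible prognostic biomarker "by demonstrating the predictive role of LTP on cognitive improvement in SCD". The Introduction (section 1) states the aim more mildly and ties it to one population: "The predictive role of the LTP-like plasticity on cognitive improvement in rTMS-treated SCD patients will be studied".

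Section 2.8 gives the only analysis for this aim: "To investigate the relationship between brain measurements and clinical cognitive function characteristics, we will perform correlation analyses by repeated measures linear regressions". Both sides of the relationship are plural. The sentence does not say which LTP value or which cognitive score decides the question, or whether the predictor is LTP at baseline or its change.

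The same section sets one general threshold: "levels of statistical significance will be set at *p* < 0.05". Its one multiplicity rule is attached to something else. After the repeated-measures ANOVA of plasticity, post hoc "comparisons between groups will be used using the Bonferroni correction method".

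On the brain side, section 2.7.2 says "The whole LTP-like plasticity assessment includes five time points": two before iTBS, and three after it at 5, 10 and 30 minutes. On the cognitive side, section 2.7.1 lists five AVLT-H scores and designates none of them. Section 2.7.2 adds the remaining tests.

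**The concern.** A verb such as *demonstrating*, joined to a biomarker claim, tells the reader that the association will be established with the usual 5% risk of a false positive. The rule as written gives that protection only if a single pair is tested. If several LTP values are set against several cognitive scores and each is read at 0.05, one chance association is enough to be reported as the promised demonstration.

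What is at stake is a secondary but prominent conclusion, that LTP-like plasticity predicts who improves. The comparison of real with sham rTMS on episodic memory does not depend on it.

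**Working it through.** **Plan's own figure.** The article states no error rate for this set of regressions. The only figure to compare with is the nominal 0.05 per test. Sidedness is not stated, so two-sided is assumed.

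**Count of cognitive scores (sections 2.7.1 and 2.7.2).**
- AVLT-H immediate, short delay, long delay, total and recognition: 5
- MoCA and MMSE: 2
- WMS-LM and DST: 2
- AFT and BNT-C: 2
- SDMT, TMT-A and TMT-B: 3
- n-back and Go/No-Go, each with accuracy and response time: 4

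The total is 5 + 2 + 2 + 2 + 3 + 4 = 18. With three post-iTBS values there are up to 18 × 3 = 54 pairs. The choice between baseline LTP and its change is not counted.

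**Expected false positives.** This number is m × 0.05 and does not depend on correlation: 5 × 0.05 = 0.25, 18 × 0.05 = 0.9, and 54 × 0.05 = 2.7.

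**Chance of at least one, independent tests.** The formula is 1 − 0.95^m. It gives 22.6% for m = 5, 60.3% for m = 18 and 93.7% for m = 54.

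**Chance of at least one, correlated measures.** The scores are related to each other, and so are the LTP time points, so the rates were simulated under the global null.
- Pearson correlations stand in for the stated regressions.
- A pair counts as significant when |r| exceeds t/√(n − 2 + t²), where t is the 97.5% point on n − 2 degrees of freedom. The cut-off is 0.361 at n = 30 (treated arm only) and 0.254 at n = 60 (both arms).
- Correlation between scores was varied from 0 to 0.7, and between LTP time points from 0.5 to 0.9. These are assumptions, because the article gives no correlations.

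| Family | Pairs | Lowest assumed correlation | Highest assumed correlation |
|---|---|---|---|
| One named pair | 1 | 5% | 5% |
| 5 AVLT-H scores × 1 LTP index | 5 | about 23% | about 15% |
| 5 AVLT-H scores × 3 time points | 15 | about 49% | about 23% |
| 18 scores × 1 LTP index | 18 | about 60% | about 28% |
| 18 scores × 3 time points | 54 | about 91% | about 42% |

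For 18 scores and one index, the rates at score correlations 0, 0.3, 0.5 and 0.7 are about 60%, 51%, 40% and 28%. Results at n = 30 and n = 60 agree to within about two percentage points, and repeated runs move individual cells by about one.

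**After correction.** One named pair returns 5%. Otherwise, Bonferroni over the listed family would need 0.05/18 = 0.0028 per test for one LTP index, or 0.05/54 = 0.0009 for three time points.

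**The case against.** The strongest reply is that this is a secondary, mechanistic analysis in a condensed article, and that choosing the index, the score and the multiplicity handling is commonly left to an analysis plan that is not shown. That is fair, and the absence of those details alone would not be a finding. The point rests on what the article does state: a conclusion in confirmatory terms, a general 0.05 threshold, and a Bonferroni rule confined to another set of comparisons. An unseen analysis plan does not alter the abstract's wording.

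A second reply is that the article treats the mechanism largely as exploratory. The abstract's Introduction speaks of exploring mechanisms, the Introduction (section 1) says only that the predictive role will be studied, LTP is a secondary outcome, and the abstract itself says only that it may be a biomarker. This stands, and it limits the point to a mismatch between one strong claim and the analysis behind it.

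Third, the calculation is not the stated analysis. A repeated-measures regression could take the three time points together, which would remove the factor of three. This also stands, and it is why the one-index rows are shown. The independent-score end is a bound rather than a realistic case, since the AVLT-H total is listed alongside its own component scores.

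A reader might infer that all 54 pairs will be tested and any one reaching p < 0.05 taken as proof. The article does not say so. It merely leaves that open.

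**Conclusion.** The point holds as a mismatch. The promise to demonstrate a predictive role is not matched by error control in section 2.8, because the number of regressions is open and the stated Bonferroni rule does not reach them.

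The size is a range. The false-positive chance runs from about 15% to 23% under the narrowest plausible reading (five AVLT-H scores, one index), through 28% to 60% (18 scores, one index), to about 42% to 91% (18 scores, three time points). It rests on two-sided 0.05 tests, the assumed correlations and Pearson tests as a stand-in.

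A reader might take 40% as a floor. The documents do not support that: with one index the rate falls to about 28% at a score correlation of 0.7, and lower still if only AVLT-H is tested. Even so, the lowest rate for an open family is about three times the nominal 5%.

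Nothing here touches the primary efficacy comparison or the sample size.

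**What to change.** Before unblinding, add to section 2.8:
- one LTP index at T0, for example the mean percent change over 5, 10 and 30 minutes after iTBS;
- the T0-to-T1 change in one named AVLT-H score;
- the population for this analysis, which the Introduction gives as rTMS-treated patients;
- a single test of that pair at two-sided 0.05.

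Label every other brain-cognition association exploratory, and report it with 95% confidence intervals or with false-discovery-rate control over the listed family.

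In the abstract, change *demonstrating* to *exploring* now. The wording should not wait on whether the named pair turns out significant. Whether such an association can establish prediction of treatment response is a separate question that error control does not settle.

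The cost is a few sentences and no new data. The downside is that an association outside the named pair can be reported only as exploratory, however striking it looks.

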**Methods:**

In our randomized, sham-controlled trial, patients (*n* = 60) with SCD will receive 20 sessions (5 consecutive days per week for 4 weeks) of real rTMS (*n* = 30) or sham rTMS (*n* = 30) over the left DLPFC. The primary outcome is the Auditory Verbal Learning Test-Huashan version (AVLT-H). Other neuropsychological examinations and the long-term potentiation (LTP)-like cortical plasticity evaluation serve as the secondary outcomes. These outcomes will be assessed before and at the end of the intervention.

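### The stated LTP–cognition analysis is a correlation; it cannot show that LTP-like plasticity predicts response to rTMS, and no endpoint supports the AD-prognosis wording

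*Protocol article*

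**What the plan says.** The aim appears in two places, with different targets.

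- Introduction, last paragraph: "The predictive role of the LTP-like plasticity on cognitive improvement in rTMS-treated SCD patients will be studied". This is worded for patients who receive rTMS.
- Abstract, Discussion: the study is said to emphasise that "impaired LTP-like cortical plasticity may be a potential biomarker of AD prognosis by demonstrating the predictive role of LTP on cognitive improvement in SCD". This is worded for SCD generally and framed as prognosis.

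Section 2.8 contains two analyses that involve LTP.

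- One is a between-group repeated-measures ANOVA to "examine LTP-like plasticity as a function of percent change at four time points". It contains no cognitive outcome.
- The other is a single sentence. Its purpose is given as "To investigate the relationship between brain measurements and clinical cognitive function characteristics", and its method as "we will perform correlation analyses by repeated measures linear regressions".

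The Abstract gives the arms as "real rTMS (*n* = 30) or sham rTMS (*n* = 30) over the left DLPFC" and the timing as "These outcomes will be assessed before and at the end of the intervention". Section 2.1 plans the cognitive and TMS assessments before and after the intervention and compares the two groups. Baseline LTP and both cognitive measurements should therefore exist in each arm.

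**The concern.** A factor that predicts response to a treatment is one across whose values the treatment effect differs. Showing this needs a comparison of real and sham at different levels of the factor. A correlation between LTP and improvement does not make that comparison.

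The AVLT-H is given twice, about four weeks apart, so some retest gain is plausible in both arms. If people with better plasticity gain more on retest whichever arm they are in, the correlation is positive among treated patients and also across both arms, although LTP carries no information about response to rTMS.

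At stake is a mechanistic claim. A correlation could be reported as LTP predicting benefit from rTMS, or as a prognostic biomarker for AD, when the data show neither.

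**Working it through.** **The plan's own figure.** No sample size is stated for the LTP aim. The only figure is 30 per group for the treatment comparison (section 2.4: d = 0.7979, alpha 0.05, power 80%, 10% added for loss). A two-sample t-test, taken as two-sided, needs 25.65, so 26 per group; 26/0.9 = 28.9, so 29. The stated 30 is reproduced to within one patient. It says nothing about the LTP aim.

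**Inputs for the illustration.** There are 30 per arm, and 30 × 0.9 = 27 if 10% are lost. The test is taken as two-sided at 0.05. The documents give no correlation between LTP and cognition, so every r below is an assumption.

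**Step 1: treated-only correlation when LTP predicts no response.** Let baseline LTP correlate r with gain equally in both arms. By Fisher's z, the chance of a significant result is approximately Φ(atanh(r)·√(n − 3) − 1.96). With n = 27, √24 = 4.899.

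- r = 0.3: 0.3095 × 4.899 = 1.516; Φ(1.516 − 1.96) = Φ(−0.444) ≈ 33%.
- r = 0.4: 0.4236 × 4.899 = 2.075; Φ(2.075 − 1.96) = Φ(0.115) ≈ 55%.

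A simulation of 20,000 trials gave 34% and 56%, and 5% at r = 0.

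**Step 2: three tests compared, 30 per arm.** Each row rests on 5,000 simulated trials with a treatment effect of 0.8 SD on gain. Entries are the percentage significant.

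| Assumed r with gain (real / sham) | Treated-only correlation | Correlation across both arms | Arm × LTP interaction |
|---|---|---|---|
| 0 / 0 | 4.7 | 5.2 | 5.0 |
| 0.3 / 0.3 (no prediction of response) | 37 | 58 | 4.6 |
| 0.5 / 0.5 (no prediction of response) | 83 | 97 | 4.4 |
| 0.5 / 0 (true prediction of response) | 83 | 44 | 50 |

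The treated-only test gives 83% in both of the last two rows, so it cannot tell them apart. The correlation across both arms is significant more often when there is no prediction of response (97%) than when there is (44%). Only the interaction stays near 5% when there is nothing to find.

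A change-on-change correlation across both arms has a further problem. If rTMS raises LTP and memory by 0.8 SD each, with no relation within either arm, it is significant in about 18% of trials.

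**Step 3: what the interaction can deliver.** Comparing the two arms' correlations by Fisher's z, SE = √(2/(n − 3)).

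- 30 per arm: SE = √(2/27) = 0.272. For 0.5 against 0, 0.549/0.272 = 2.018; Φ(2.018 − 1.96) ≈ 52% power.
- 27 per arm: SE = √(2/24) = 0.289. For the same contrast, 0.549/0.289 = 1.903; Φ(1.903 − 1.96) ≈ 48% power.
- For 0.3 against 0, power is about 21% (30 per arm) or 19% (27 per arm).
- The contrast detectable with 80% power at 30 per arm has Fisher-z size 2.80 × 0.272 = 0.762, which is r = 0.64 against 0.

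**Step 4: the prognosis wording.** Section 2.1 places the outcome assessment at completion of the intervention (T1). No later visit or progression endpoint is stated. The data can describe change over about four weeks and cannot address progression to AD.

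**The case against.** The strongest reply is that one sentence in a condensed article does not fix a model. A repeated-measures regression can contain arm, time and interaction terms, and such detail is often left to the full plan. This limits what can be said, and three stronger readings should not be drawn.

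- A reader might infer that the arms will be pooled without an arm term. Section 2.8 does not say how the arms are handled.
- A reader might infer that the sham arm will not be used. Only the Introduction words the aim for treated patients; the Abstract does not, and section 2.8 states an intention-to-treat analysis. Nothing excludes sham patients.
- A reader might infer that the regression estimates only same-visit association. That depends on which LTP value is paired with which cognitive score, and this is not stated.

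The figures also rest on assumed correlations, and 27 per arm counts completers although multiple imputation is planned. LTP is a secondary outcome, and the biomarker phrase is partly hedged. The interaction will often be inconclusive.

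All of this stands, but it does not remove the mismatch. The article states a method for this aim, describes its purpose as a relationship, and attaches to it a claim of demonstrated prediction. Neither a treated-only nor a both-arm correlation supports that claim. Unstated model terms cannot rescue the AD-prognosis wording, because the stated outcomes end at T1.

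**Conclusion.** The concern holds as a mismatch between aim and stated analysis. The article promises prediction, with one target in the Introduction and another in the Abstract, and states only a correlation. Under assumed equal correlations of 0.3 or 0.4 in both arms, a treated-only test with 27 patients is significant in about 33% or 55% of trials with no prediction of response. With no prognostic relation the rate is the nominal 5%. The analysis therefore could mislead; it would not necessarily do so. The logic does not depend on the values chosen, but the percentages do.

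This is a worthwhile, inexpensive correction to a secondary aim. It does not touch the primary efficacy comparison or the sample size. The documents do not establish that a pooled or a treated-only analysis is what will be run.

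**What to change.** **Section 2.8.** For this secondary aim, specify one model in all randomised patients: T1 AVLT-H on T0 AVLT-H, arm, T0 LTP and arm × T0 LTP. Name in advance which of the AVLT-H scores in section 2.7.1 is used, and which single summary of the post-iTBS measurements in section 2.7.2 stands for LTP. Then report:

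- the interaction with its 95% CI, as the exploratory test of prediction of response;
- the T0 LTP term, as prognostic for the 4-week change only (with the interaction in the model, state the arm or the average to which it refers);
- the correlations, including change on change, as descriptive.

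If the full plan already contains this model, it is enough to say so in section 2.8.

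**Introduction and Abstract.** Use the same target in both. In the Abstract's Discussion, replace 'demonstrating' with 'exploring' and remove the AD-prognosis claim.

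**Cost.** One additional model and some wording; no new data, since LTP and cognition are already planned in both arms. The downside is a wide interaction interval with about 27 to 30 per arm: power is about 50% for 0.5 against 0, and 80% would need about 56 per arm. The result has to be presented as exploratory. If that is unwelcome, the alternative is to restate the aim as an association.
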